### Interventions

Eligible participants will receive an Antianxiety Granule or placebo treatment twice daily for 6 weeks according to their random assignment. The Antianxiety Granule is composed of *Cyperi rhizoma*, *Amomum aurantiacum*, *Cinnamomi cortex*, *Curcumae radix*, *Radix salviae*, *Gardeniae fructus*, *licorice*, *Polygala tenuifolia*, *Albizia bark*, *Polygoni multiflori caulis*, and *Daylily.* The herbs will be mixed into brown, bitter, herbal extract granules, and the placebo will consist of one-tenth of the Antianxiety Granule. Both the Antianxiety Granule and placebo will have an identical appearance, colour, and smell. All granules will be packaged in sealed, opaque single-dose sachets with similar labelling. Participants will receive two packaged dose bags (14 doses per bag) every 2 weeks, three times in total, and they will be requested to return the unused granules to the research teams. The use and returning of the granules will be noted on the case report forms (CRFs) by the researchers. All participants will receive some transportation allowances at the end of the trial.

### Outcomes

#### Primary outcome

The primary outcome measure will be a change in the HAMA score [19]. The HAMA scale is the most widely used assessment tool for anxiety disorders in psychiatric clinical and scientific research. The HAMA scale is a 14-item observer-rating questionnaire that can be categorized into two orthogonal groups, “psychic” and “somatic” anxiety. The outcome will be assessed by the difference in the HAMA score from the baseline.

#### Secondary outcomes

Secondary outcomes include the STAI score and TCM symptom scale. The STAI is used extensively in research and provides a reliable self-reported scale for measuring emotional state (S-Anxiety) and personality traits (T-Anxiety) [20]. The STAI consists of two 20-item scales (state anxiety inventory (S-AI) and trait anxiety inventory (T-AI)). The S-AI is used to assess the intensity of anxiety as a transitory emotional state, and the T-AI is used to measure anxiety as a relatively stable personality trait. Each item has a 1–4 score rating. The higher the total score, the more severe the anxiety [21].

The TCM symptom scale will be used to assess the improvement of symptoms but symptom improvement will not be scored. The improvement of symptoms is defined as a reduction in the number of symptoms from enrolment to the end of the study. Each patient is required to record any change in symptoms on the CRF. The researcher will assess the change in symptoms at each visit.

### Safety assessment and adverse events

Safety will be monitored throughout the trial. Routine laboratory safety tests (including routine tests of blood, urine, liver function (ALT, AST), and kidney function (blood urea nitrogen (BUN) and creatinine (Cr)) will be performed at the screening visit and visit 5. Safety will also be assessed through monitoring adverse events (AEs) and vital signs throughout the 6 weeks of treatment. AEs are defined as unexpected symptoms, signs, or diseases that occur during treatment, and all participants will be instructed to report any abnormal event. If AEs happen, the investigators will evaluate the relationship between the AE and the intervention. All AEs will be reported in detail on the CRF. The schedule of enrolment, interventions, assessments, and data collection is presented in Table 1.

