## Abstract

**Background:**

Anxiety disorders are the most prevalent class of lifetime disorders in China, and generalized anxiety disorder (GAD) is one of the most common but frequently overlooked anxiety disorders. Conventional pharmacological treatments for GAD have varying degrees of side effects, dependency, and/or withdrawal syndromes. Traditional Chinese medicine (TCM) is considered a valuable therapeutic option for anxiety disorders and a potentially effective technique to reduce the side effects associated with antipsychotic drugs. This trial aimed to evaluate the clinical efficacy and safety of Antianxiety Granule, a granular Chinese medicine compound, for treatment of GAD.

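### The adverse event definition covers only unexpected events during treatment, which conflicts with the same section's trial-wide safety monitoring and with the 1-week follow-up

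*Protocol article*

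**What the plan says.** All the key statements are in the protocol article, section Safety assessment and adverse events.

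- Scope: "Safety will be monitored throughout the trial".
- AE monitoring window: "Safety will also be assessed through monitoring adverse events (AEs) and vital signs throughout the 6 weeks of treatment".
- Definition: "AEs are defined as unexpected symptoms, signs, or diseases that occur during treatment".
- Instruction to participants: "all participants will be instructed to report any abnormal event".
- Recording: "All AEs will be reported in detail on the CRF". The investigators' judgement of relationship to the intervention is likewise stated for AEs.
- Laboratory safety tests: "will be performed at the screening visit and visit 5".

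Setting and design gives three periods: screening of 1 to 7 days, 6 weeks of treatment and 1 week of follow-up. The follow-up assessment takes place 1 week after the last visit, in person or by telephone. The Abstract gives the motivation for the product: "Conventional pharmacological treatments for GAD have varying degrees of side effects, dependency, and/or withdrawal syndromes".

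**The concern.** The definition sets two conditions, and both are narrower than the rest of the section.

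The first is type. An event must be unexpected to count. Expectedness is normally a property recorded for an AE after it has been captured, not a test for whether it is one. The definition also names symptoms, signs and diseases but does not say whether an abnormal result from the scheduled laboratory tests counts.

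The second is time. An event must occur during treatment, and AE monitoring is set to the 6 treatment weeks, although the trial runs on to a follow-up contact.

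Safety is a stated objective alongside efficacy. The article argues for the granule partly by pointing to the side effects, dependency and withdrawal problems of existing drugs. Anticipated reactions and events after stopping are the two classes that bear most directly on that comparison, and they are the classes the definition leaves out. A site or analyst following the definition literally could omit them, while one following the opening sentence would include them. In a multicentre trial, different sites could resolve the conflict differently.

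**Working it through.** No figure in the plan depends on this definition, so there is nothing to reproduce. The check is a comparison of the text plus one line of arithmetic.

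**Step 1: which events count.** The definition admits unexpected events only. The instruction to participants covers anything abnormal. CRF recording and the relationship assessment are stated for AEs. A participant may therefore report an event, as instructed, that the site need not enter or assess as an AE because it was anticipated.

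**Step 2: when events count.** The opening sentence covers the whole trial. The definition and the monitoring sentence cover treatment only. From Setting and design:

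- weeks from start of treatment to end of follow-up: 6 + 1 = 7
- weeks inside the AE window: 6
- weeks outside it: 7 − 6 = 1, or 1/7 ≈ 14% of the time

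For a participant who completes treatment, that week is the only scheduled time off the granule. The 14% is a share of calendar time. It does not estimate the share of events lost.

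**Step 3: whether other text closes the gap.**

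- The laboratory tests at visit 5 might fall in the follow-up week, but the text does not tie visit 5 to a week. If screening and baseline are one visit, weeks 2, 4 and 6 are visits 2 to 4 and visit 5 is the follow-up contact. If they are separate visits, visit 5 is week 6. Table 1, which would settle this, is not shown.
- Secondary outcomes has each patient record symptom changes on the CRF for the TCM symptom scale. This is a possible second channel, but it serves an efficacy outcome and may be limited to symptoms on that scale.
- The safety set in Statistical analyses defines which participants are included. It sets no window for events.

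Nothing in the visible text overrides the two restrictions.

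**The case against.** The strongest reply is that loss of data is not demonstrated. The 6-week sentence says safety will *also* be assessed in this way, so it can be read as adding to trial-wide monitoring rather than limiting it. With the instruction to report anything abnormal, this suggests wider capture in practice. The word *unexpected* may be loose wording for *untoward*: the article lists no expected reactions, so the excluded class has no named members. No outcome or hypothesis concerns withdrawal from the granule. Separate expectedness fields and post-treatment tables are details that an article commonly leaves to the full protocol, the CRF or the SAP.

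Much of this stands as a limit on the claim. A reader might infer that no AEs will be collected in the follow-up week, or that withdrawal effects are removed from the safety data altogether. The article does not support that, because Table 1 is not shown and the broader sentences point the other way. A reader might also infer that the granule will look safer than it is. That would require expected reactions that differ between arms, and the article gives no evidence of any; recording is also double-blind.

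The reply does not remove the inconsistency. The article does not leave the definition to another document; it states one. Even if *unexpected* is read as *untoward*, the restriction to treatment time remains and conflicts with the opening sentence.

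**Conclusion.** The point holds as an internal contradiction with a possible effect on safety ascertainment. As written, anticipated reactions and events that begin in the 1-week follow-up need not be recorded as AEs or assessed for relationship, so AE counts could be too low.

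The number of events affected, and the size and direction of any difference between arms, cannot be determined from the article. The only figure available is the time window, 1 week of 7.

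The conclusion assumes that sites or analysts would apply the definition literally. If they follow the broader sentences instead, the loss could be small or nil. Because the effect is possible rather than shown, and neither randomization nor the primary efficacy analysis is touched, this is a should-fix and not a must-fix.

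**What to change.** Reconcile the section around one definition and one window:

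- Define an AE as any untoward symptom, sign, clinically significant abnormal laboratory finding or disease from first dose to the end of the 1-week follow-up, regardless of expectedness or relatedness.
- Record expectedness and relatedness as separate attributes of each AE.
- Ask about AEs at the follow-up contact, whether in person or by telephone.
- Report on-treatment and post-treatment AEs separately by arm.

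The cost is minor wording changes to the protocol and CRF, a note to sites, and a few minutes at a contact that is already scheduled. Recruitment is described as ongoing, so events before the change may be under-recorded. A check of source notes for participants already treated would show how far, and the report should state the date of the change.

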### Quality control

The study will be conducted at five hospitals to guarantee its rigour and quality. The investigators will be trained to ensure the quality of the trial. All of the trial data will be fully integrated into the CRFs and monitored by the Clinical Research Centre of Drugs of the Shanghai Municipal Hospital of Traditional Chinese Medicine. Moreover, if any inconsistent data are identified, the primary data will be individually checked by the research monitor and the inconsistency will be reported. The database will be locked after it is reviewed and confirmed by the administrator and the inspector. The source data will be saved appropriately and patient-reported treatment guesses will be obtained to determine the success of blinding. Fisher’s exact test will be used to analyse the data.

### Statistical analyses

The main analysis will follow the intention-to-treat (ITT) principle and will be done as follows: the full analysis set (FAS) will include the randomized participants who received any treatment and completed at least one follow up. The per-protocol set (PPS) will include patients who complied with the protocol. Only when the minimum compliance rate of participants who received the investigational drug is 80% will we use the PPS. Participants who have at least one randomized treatment will be included in the ITT and safety set (SS). To estimate missing primary outcome variables, data from the last study will be used as the final result following the last observation carried forward (LOCF) principle. Data will be analysed using the statistical software SAS version 9.4 or SPSS 20.0.

Sociodemographic variables will be analysed by the *t* test for continuous variables. Matched data will be compared using the Wilcoxon test, and categorical variables will be analysed using the chi-squared test. Change across time of the primary and secondary outcomes will be analysed by repeated measures analysis of variance (ANOVA). We will use ANOVA for randomized block design if the variance and covariance matrix meet the sphericity assumption. ANOVA for repeated measurement data may have two types of error: errors among subjects are the errors corresponding to treatment, and errors within subjects are the errors corresponding to time and the interaction between treatment and time. Significance is will be accepted when the two-sided alpha level is 0.05.

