### Sample size

A sample size of 252 participants will be recruited on the basis of the pre-post trial. On the basis of previous results and considering an anticipated participant dropout rate of 20%, with a significance level of 0.05, 252 patients will be needed. These 252 patients will be randomly divided into two groups (168 participants in the Antianxiety Granule group and 84 participants in the placebo group, in a ratio of 2:1).

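### The only missing-data rule covers HAMA, yet STAI and the TCM symptom outcome are assigned a classical repeated-measures ANOVA that, in its standard form, drops participants with incomplete visits

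*Protocol article*

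**What the plan says.** All references are to the protocol article.

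- **Primary outcome:** "The primary outcome measure will be a change in the HAMA score".
- **Secondary outcomes:** "Secondary outcomes include the STAI score and TCM symptom scale". For the TCM scale, "The improvement of symptoms is defined as a reduction in the number of symptoms from enrolment to the end of the study". The researcher also reviews symptom change at every visit.
- **Statistical analyses, missing data:** "To estimate missing primary outcome variables, data from the last study will be used as the final result". The method named is LOCF. No section gives a rule for STAI or the TCM scale.
- **Statistical analyses, method:** "Change across time of the primary and secondary outcomes will be analysed by repeated measures analysis of variance (ANOVA"). The text then makes the analysis conditional on sphericity. It separates a between-subject error (for treatment) from a within-subject error (for time and treatment-by-time).
- **Statistical analyses, sets:** "The main analysis will follow the intention-to-treat (ITT) principle". The FAS takes randomised participants with any treatment and one or more follow-ups; the ITT set needs only one randomised treatment. Neither requires a full set of visits.
- **Sample size:** 252 participants, 168 and 84, "considering an anticipated participant dropout rate of 20" per cent.
- **Setting and design:** assessments at baseline and weeks 2, 4 and 6.

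**The concern.** For the secondary outcomes, these statements do not fit together. The ANOVA described is a complete-data method in its usual implementation. For HAMA, LOCF supplies the missing visits. For STAI nothing does, although the FAS deliberately admits people with only one follow-up. The TCM outcome is defined at the end of the study, which a dropout does not reach.

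Two things are at stake. First, completers are a group selected after randomisation, so the comparison of arms on STAI and symptoms loses the protection of randomisation if the reasons for leaving differ by arm. Second, week 2 and week 4 data already collected would be thrown away, and the secondary results would describe a different group of patients from the primary result.

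**Working it through.** **1. The plan's own figure.** The 2:1 split reproduces: 252 × 2/3 = 168 and 252 × 1/3 = 84. The total of 252 cannot be reproduced, because the article gives no effect size, SD or power. Both 201 / (1 − 0.20) = 251.25, rounded up to 252, and 210 × 1.20 = 252 are possible. Either way, the 252 already contains an allowance for dropout.

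**2. How many are affected.** At 20% dropout:

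- lost: 252 × 0.20 = 50.4 (33.6 Granule, 16.8 placebo)
- retained: 252 × 0.80 = 201.6 (134.4 and 67.2)

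About 50 is an upper limit for dropouts who are in the FAS, because anyone lost before a first follow-up is not in it (taking a follow-up to mean any post-baseline visit). Completers who skip a middle visit would add to the number; the article gives no basis for counting them.

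**3. One participant traced through the plan.** Take someone seen at baseline, week 2 and week 4, then lost.

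| Outcome | Week 6 value under the stated rules | Result |
|---|---|---|
| HAMA | week 4 value carried forward | analysed |
| STAI | none stated | dropped if the ANOVA is run on complete records |
| TCM improvement | no end-of-study count | outcome undefined |

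This person belongs to the FAS throughout.

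**4. Precision.** The SE ratio against full retention is sqrt(1 / (1 − d)): 1.054 at d = 0.10, sqrt(252 / 201.6) = 1.118 at 0.20, and 1.195 at 0.30. A mixed model would recover less than this 12%, since dropouts supply only part of their visits.

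**5. Bias, illustrated.** The documents give no dropout rates by arm, so every input here is an assumption.

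- *No true effect; 168 and 84; SD 1; correlation 0.6 between all visits; dropout after week 2.* With unrelated 20% dropout in both arms, completers show a week 6 difference of 0.00 SD. Next, dropout stays unrelated in the Granule arm, while in the placebo arm its log-odds are −1.6 + 1.0 × (week 2 score above its mean, in SD). About 201 are retained, and placebo dropout is (252 − 200.95 − 33.6) / 84 = 20.8%. The completers' week 6 scores now differ by +0.10 SD (against Granule), while their change from baseline differs by 0.00 SD. So bias can appear at nearly equal dropout rates, and it depends on the quantity compared.
- *True week 6 difference of −4 points, about 20% dropout.* Completers gave −4.0 with unrelated dropout and −3.8 with poor responders leaving both arms. They gave −2.2 with 17% unrelated dropout in the active arm and 30% among poor responders in the control arm. These figures also depend on a variance and correlation that the documents do not supply, so they show direction only.

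**6. TCM improvement.** Assume 70% against 55% improved among completers, a 15-point difference. Counting dropouts as not improved gives 0.70 × (1 − dA) − 0.55 × (1 − dC):

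- dA = dC = 0.20: 0.560 − 0.440 = 12 points
- dA = 0.15, dC = 0.30: 0.595 − 0.385 = 21 points
- dA = 0.25, dC = 0.10: 0.525 − 0.495 = 3 points

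All three keep overall dropout at 20% (for example, 168 × 0.15 + 84 × 0.30 = 50.4). The lines use a different outcome definition from the completers' figure, so they do not measure bias. They show how far the result depends on a choice the article leaves open.

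**The case against.** The strongest reply is that this is silence in a condensed article, and that missing secondary data are normally handled in the full protocol or SAP, neither of which is shown. Silence alone would indeed be no finding. But the article goes further: it restricts its rule to one outcome and names a complete-data method for the others. A later document could cure that only by adding to or changing what is written.

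Other points stand and limit the concern:

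- **Deletion is inferred from the method.** No procedure is named, only SAS 9.4 or SPSS 20.0. The randomised-block form that the article mentions, fitted with one row per visit, could keep partial records. The article does not say that it will be fitted so.
- **A reader might infer that a completers-only analysis is being presented as ITT.** The text attaches ITT to the main analysis and does not label the secondary analyses.
- **A reader might infer that dropouts have no secondary data.** They may have week 2 and week 4 values; only later ones are missing.
- **The contrast of 252 with 202 is not a shortfall against plan.** The sample size allows for 20% dropout, and the FAS may itself fall below 252.
- **Changing only the secondary analyses leaves HAMA on LOCF.** Methods would then differ between outcomes, although the same patients would contribute. Whether LOCF suits HAMA is a separate question.

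**Conclusion.** The point holds for the secondary outcomes only. The stated rule and the stated method leave incomplete STAI and TCM records without a defined place in the analysis. The natural reading of the method would exclude up to about 50 of 252 participants and discard visits they attended. This rests on the article's 20% dropout figure and on the standard implementation of the classical ANOVA.

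Precision is a minor matter: at most a 12% larger SE than with full retention, which the plan never assumed. Bias is small where dropout is similar across arms and could be material where it differs by arm and response. A reader might take the −2.2 against −4.0 result as showing that (4.0 − 2.2) / 4.0 = 45% of the effect would be lost. The documents do not support that: it comes from a chosen arm-specific dropout pattern that they nowhere state. The primary HAMA analysis, with LOCF, does not become completers-only.

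**What to change.** In Statistical analyses:

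1. **STAI.** Replace repeated-measures ANOVA with a likelihood-based mixed model for repeated measures, using all observed values at baseline and weeks 2, 4 and 6. State which of the sets already defined (FAS or ITT) it uses.
2. **TCM symptom improvement.** Impute a missing end-of-study count by multiple imputation from the counts recorded at each visit. Add a sensitivity analysis that counts dropouts as not improved.
3. **Sensitivity for STAI.** The mixed model assumes data are missing at random. Add an analysis that departs from this assumption for STAI as well, so that it is examined for both outcomes.

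The cost is revised wording and a little more programming in SAS 9.4, which the article already names. No new data, visits or patients are needed. The drawback is reliance on missing at random: if leaving depends on unrecorded response, the mixed model does not remove the bias, which is why the sensitivity analyses belong in the plan.

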## Methods/design

### Setting and design

This study is a multicentre, randomized, double-blinded, placebo-controlled, parallel-group, 6-week treatment, clinical trial. Eligible participants will be randomly assigned to an intervention group (Antianxiety Granule) or placebo group at a ratio of 2:1. The participants will be recruited from the following six hospitals: Shanghai Municipal Hospital of Traditional Chinese Medicine, Shanghai Seventh People’s Hospital, Shanghai Chinese and Western Medicine Hospital, The Fifth People’s Hospital of Shanghai, Fudan University, Jingan District Hospital of Traditional Chinese Medicine, and Yangpu District Hospital of Traditional Chinese Medicine. The study consists of three periods: a 1–7-day screening period, a 6-week primary treatment period, and a 1-week follow-up period. Participants will be assessed at baseline and at the 2nd, 4^th^, and 6th week after the initiation of the intervention. Follow-up assessments will be conducted 1 week after the last visit by face-to-face interviews or by telephone (Fig. 1). In this study, the clinical efficacy of Antianxiety Granule will be assessed for the treatment of GAD by examining changes in the Hamilton anxiety scale (HAMA) score, state-trait anxiety inventory (STAI) score and the TCM symptom scale in patients with GAD who receive daily TCM treatment. The flowchart of the study process is presented in Fig. 1, and the timing of the treatment visits and data collection is presented in Table 1.

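### The primary HAMA analysis fixes no week and no deciding term, states no adjustment for baseline or centre, and has a sphericity switch that does not fit its own error terms

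*Protocol article*

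**What the plan says.** Under Primary outcome, the article defines the endpoint without a time point: "The outcome will be assessed by the difference in the HAMA score from the baseline". Setting and design lists assessments at baseline and weeks 2, 4 and 6, with a follow-up one week later, in person or by telephone.

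Under Statistical analyses, the method for all efficacy outcomes is: "Change across time of the primary and secondary outcomes will be analysed by repeated measures analysis of variance (ANOVA". It continues: "We will use ANOVA for randomized block design if the variance and covariance matrix meet the sphericity assumption". The following sentence describes two error strata: between-subject error for treatment, and within-subject error for time and treatment-by-time. The test level is also given: "Significance is will be accepted when the two-sided alpha level is 0.05".

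Randomization is stratified by centre (Randomization, allocation, and blinding), but neither centre nor baseline HAMA appears in the stated analysis. The planned numbers are "168 participants in the Antianxiety Granule group and 84 participants in the placebo group, in a ratio of 2:1", with 20% dropout allowed for.

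**The concern.** A repeated-measures ANOVA with treatment, time and their interaction gives three F tests. Two of them, treatment and treatment-by-time, compare the arms, and they answer different questions. The first compares the arms on an average over visits. The second asks whether the arms' profiles diverge at all, on several degrees of freedom. Neither is the difference at the end of treatment, and the plan does not say which one decides.

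The visits that enter the model are not stated either. If raw HAMA at baseline is one level of the time factor, the treatment main effect averages in a visit at which randomized arms have no expected difference.

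The sphericity sentence adds a second difficulty. In a randomized-block ANOVA with the subject as block, treatment is constant within each block, so it cannot be tested against the block residual. That does not fit the next sentence, which gives treatment the between-subject error. It also makes the form of the primary analysis depend on a check of the trial's own data.

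At stake are the power of the trial's one primary comparison and what a significant result would mean.

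**Working it through.** **The plan's own figure.** 168 + 84 = 252, ratio 2:1. After 20% dropout, 168 × 0.8 = 134.4 and 84 × 0.8 = 67.2, so about 134 and 67 completers. In reverse, 201 / 0.8 = 251.25, rounded up to 252. The effect size, SD and power behind 252 are not stated, so the figure cannot be reproduced beyond this arithmetic.

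**Assumptions (none is in the article).** HAMA has SD 1 at every visit, with equal correlation ρ between visits (compound symmetry) of 0.3, 0.5 or 0.7. The week-6 effect is the one that 201 completers detect with 80% power in a simple comparison at a single visit. With √(1/134 + 1/67) = 0.1496, that is (1.960 + 0.842) × 0.1496 = 0.419 SD. This value is back-solved, not taken from the plan. Linear build-up means 0, 1/3, 2/3 and 1 of the effect at baseline and weeks 2, 4 and 6.

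**Formula.** z = (effect in the contrast) / (SD of the contrast × 0.1496). Power is about Φ(z − 1.96).

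- *A. Treatment main effect, raw baseline and weeks 2, 4, 6.* Mean effect (0 + 1/3 + 2/3 + 1)/4 = 0.5 of 0.419 = 0.2095. SD = √((1 + 3ρ)/4) = 0.689 / 0.791 / 0.880. z = 2.03 / 1.77 / 1.59.
- *B. Treatment main effect on change scores at weeks 2, 4, 6, linear build-up.* Mean effect 2/3 of 0.419 = 0.279. SD = √((1 + 2ρ)/3 + 1 − 2ρ) = 0.966 / 0.816 / 0.632. z = 1.93 / 2.29 / 2.95.
- *C. As B, with the full effect from week 2.* Effect 0.419, same SD. z = 2.90 / 3.43 / 4.43.
- *D. Week-6 change, unadjusted.* SD = √(2(1 − ρ)) = 1.183 / 1.000 / 0.775. z = 2.37 / 2.80 / 3.62.
- *E. Week-6 change adjusted for baseline.* SD = √(1 − ρ²) = 0.954 / 0.866 / 0.714. z = 2.94 / 3.23 / 3.92.
- *F. Treatment-by-time interaction, 3 df, linear build-up.* Noncentral F on 3 and 3 × (201 − 2) = 597 df.

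| Test | ρ = 0.3 | ρ = 0.5 | ρ = 0.7 |
|---|---|---|---|
| A | 53% | 42% | 36% |
| B | 49% | 63% | 84% |
| C | 83% | 93% | 99% |
| D | 66% | 80% | 95% |
| E | 84% | 90% | 98% |
| F | 53% | 69% | 91% |

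Using t in place of normal quantiles moves A, D and E by about a percentage point or less.

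**The block sentence.** With between-subject error for treatment, as the plan's next sentence says, simulated type I error was 4.7–5.1% (10,000 runs per ρ). Only if treatment were tested against the within-subject residual would the variance ratio be (1 + 3ρ)/(1 − ρ) = 2.71 / 5.00 / 10.33. Type I error would then be 2 × (1 − Φ(1.96/√ratio)) = 23% / 38% / 54%.

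**The case against.** Three stronger readings are tempting, and the document supports none of them.

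*The plan uses the wrong error term.* It does not say so. The sentence after the switch gives treatment its correct error. The randomized-block sentence may mean only that, under sphericity, the ordinary uncorrected F tests apply to time and the interaction. The 23 / 38 / 54% figures need a literal single-error reading.

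*Efficacy will be judged on change within an arm.* The model contains two between-arm terms, and the Discussion states the purpose as a comparison with placebo. The sentence "Matched data will be compared using the Wilcoxon test" is not tied to HAMA; the efficacy outcomes get their own sentence. The phrase "in patients with GAD who receive daily TCM treatment" is loose description, not an analysis rule.

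*Type I error doubles.* 1 − 0.95² = 9.75% applies only if success on either of two independent tests counts, which the plan nowhere says.

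There are two fair objections to the power figures. The loss depends on effect shape: with the full effect from week 2, row C is about level with row E. Part of the gap between A and E is baseline adjustment rather than choice of week, as row D shows. It is also fair that covariates, the ordering of model terms and the procedure when sphericity fails are often left to an analysis plan, and none is shown here.

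What remains is that the article does set out its primary analysis, down to error strata and a switching rule, and in that form it fixes neither the week nor the comparison. Carrying the last observation forward to a final result hints at an end-of-treatment endpoint, but nothing links it to the ANOVA or to week 6.

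**Conclusion.** The point holds in limited form, as an improvement available at no cost rather than an error that invalidates the trial. The primary HAMA comparison has no named week and no deciding term, the stated model uses neither baseline HAMA nor the stratification factor, and the randomized-block sentence does not fit the plan's own error strata.

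Under linear build-up, the choice left open moves power from 53 / 42 / 36% (row A) to 84 / 90 / 98% (row E). If the effect is full from week 2, averaging change scores loses little or nothing. These sizes rest on the assumed effect, its shape, the correlation structure and the completer numbers; the article gives none of them beyond the sample size, allocation and dropout rate. The ambiguity itself does not depend on those assumptions.

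**What to change.** Before unblinding:

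1. Name one primary test: the between-arm difference in HAMA change from baseline to week 6, at two-sided 0.05.
2. Estimate it by ANCOVA at week 6, or by a mixed model for repeated measures on weeks 2, 4 and 6 with the treatment difference taken at week 6. Either is acceptable, with baseline HAMA and centre as covariates.
3. Delete the sphericity-dependent randomized-block sentence.
4. State that other visits, the time effect and any within-arm test are descriptive and carry no efficacy claim.

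This changes wording only. The visits, data, software and number of patients stay the same.
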